**Fig. 4 Fig4:**

Structural equation model of the direct and indirect effects of perception of compassion on PTSD symptoms

### Sample size justification

Our sample size is designed to detect a difference in the proportion of patients experiencing AWP in the control versus the intervention phase. The sample size must be inflated by estimating the design effect, to account for the intraclass correlation coefficient (ICC). More common outcomes are associated with higher design effects, whereas lower prevalence outcomes, such as AWP, have smaller ICCs [94]. Based on our data, and extensive supporting analyses from more than 100 ICC values obtained from research studies and population health outcomes analyses (*n* > 1,000,000 patients) which show a strong linear association between the ICC and outcome prevalence in clustered binary data, we conservatively estimate an ICC of 0.001 [94]. From our preliminary multicenter data, due to a reduction in rocuronium use, it is reasonable to estimate a reduction in the proportion of patients experiencing AWP from 4.0% in the control phase to 0.2% in the intervention phase (data from the operating room), which would require a total sample size of 1650 patients [95]. To err on the side of conservative assumptions, and to account for possible non-adherence during the study, we will assume a prevalence of AWP of 3.3% in the control phase and 0.6% in the intervention phase. These conservative estimates are based on our prior work (control phase), and the intervention phase event rate is similar to that seen in operating room patients managed with total intravenous anesthesia and when longer-acting NMB is limited [10, 19, 96]. Thus, these calculations are both clinically important (would prevent ~ 10,000 AWP cases annually in the USA) and plausible from supporting preliminary work. Considering there are 5 sites and 6 time periods, for 80% power with *α* of 0.05, we will need a total sample size 3090 patients.

With respect to PTSD, if we estimate that PTSD occurs in 45% of those with AWP [5, 6, 9] and 20% of the rest of the cohort [25–27], assuming *α* = 0.05 and power = 0.80, using two-sided *Z*-test with pooled variance, a sample size of 1192 patients will be required for the multivariable model above. With respect to perceived threat, even if correlation between perceived threat and PTSD symptoms is smaller than our prior work (0.3) then a minimum of 412 patients is estimated to detect the mediated effect of perceived threat between clinician compassion and PTSD symptoms [38, 97, 98].

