**Fig. 2 Fig2:**

Example novel paradigm and hypothesized causal pathway for improving patient-centered outcomes. It is possible that by addressing the early period of critical illness in the emergency department, modifiable targets (increasing provider compassion, decreased patient-perceived threat, preventing awareness with paralysis) can be used to improve patient-centered clinical outcomes

There is significant rationale to target rocuronium use in the ED as a means to prevent AWP. In the ED-AWARENESS Study and ED-SED Pilot Trial, 19/23 (92.6%) AWP patients received rocuronium [19, 23]. In multivariable analysis, rocuronium was independently associated with AWP (adjusted odds ratio, 6.05; 95% CI, 1.46–17.56) [19, 23]. Importantly, AWP was not associated with other sedation-related variables, including (1) sedation monitoring; (2) analgesics, sedatives; or (3) sedation depth. This confirms that a proposal to target ED-based rocuronium may have the greatest chance to improve safety and prevent AWP. This is critical as data from the National Emergency Airway Registry (*n* = 17,583) show rocuronium use was 5% for intubations in 2002, yet up to ~ 45% by 2012 [14]. Use was up to 49% in our ED SED Study, and 60% in the ED-SED Pilot Trial [17, 21]. This indicates that AWP is likely a growing health problem. Contrary to a 5-min duration of succinylcholine (the historical default NMB), rocuronium can paralyze for up to 150 min, greatly increasing AWP risk. In addition, in clinical trials comparing rocuronium versus succinylcholine, with respect to intubating conditions, data has either favored succinylcholine or shown no difference in outcomes [43–45]. However, other preliminary work from our research team did not show an association between rocuronium and AWP risk, but rather pre-intubation mental status [24]. This suggests equipoise in the data and further confirms the need for this large-scale clinical trial.

Our objective is to conduct a pragmatic clinical trial aimed at limiting rocuronium exposure in order to reduce the proportion of mechanically ventilated ED patients experiencing AWP. We hypothesize that limiting rocuronium exposure in the ED, using succinylcholine as the default NMB of choice, will significantly reduce the proportion of patients experiencing AWP.

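### The 0.6% intervention-phase AWP rate is called conservative and allowing for non-adherence, yet the protocol's own ED figures give point estimates above it even with no rocuronium use

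*Protocol article*

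**What the plan says.** Protocol article, Sample size justification: a scenario of 4.0% versus 0.2% is put at 1650 patients. The plan then moves to the rates it uses: "we will assume a prevalence of AWP of 3.3% in the control phase and 0.6% in the intervention phase". These are presented as the cautious choice: "To err on the side of conservative assumptions, and to account for possible non-adherence during the study, we will assume a prevalence of AWP". The 0.6% is referred to operating-room experience with total intravenous anesthesia and limited longer-acting NMB. The ICC is 0.001. The result is "Considering there are 5 sites and 6 time periods", "for 80% power with *α* of 0.05", "we will need a total sample size 3090 patients".

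Protocol article, Background: AWP occurred in 10/306 and 13/314 survivors given NMB in two ED studies. Across these, "19/23 (92.6%) AWP patients received rocuronium", and "rocuronium was independently associated with AWP (adjusted odds ratio, 6.05; 95% CI, 1.46–17.56"). On baseline use: "Use was up to 49% in our ED SED Study, and 60% in the ED-SED Pilot Trial". A further cohort, with AWP in 7.4%, found no link between rocuronium and AWP.

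Interventions, Informed consent and Proposed statistical methods: the intervention is a nudge, the treating team keeps the final choice of drug, and the analysis is by intention to treat whatever the adherence.

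**The concern.** The intervention is meant to lower AWP by lowering rocuronium use. The rate expected with no rocuronium at all is therefore the best the hypothesized mechanism can deliver, and clinicians who keep using it pull the intervention-phase rate back toward control. A rate described as allowing for non-adherence should lie above that best case. On the protocol's own ED point estimates, 0.6% lies below it.

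What is at stake is how a null result would be read. With partial adherence the power may be well under 80%, while the text invites readers to treat a non-significant result as an adequately powered negative.

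**Working it through.** **1. Reproduce 3090.** The protocol does not name its formula. The Hussey–Hughes stepped-wedge variance, with 5 sites, 6 periods and one site crossing per step from period 2, reduces to

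Var = 5s²(s² + 6τ²) / (20s² + 70τ²),

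where s² = p(1−p)/m at the control rate, τ² = 0.001·p(1−p), and m is patients per site-period. With p = 0.033 and m = 103: s² = 0.031911/103 = 0.000310, τ² = 0.0000319, Var = 0.0000921, SE = 0.0096. Then 0.027/0.0096 = 2.81, less 1.96 is 0.85, so power is 0.80 (two-sided 0.05). Solving for 80% gives m = 102.04, rounded up to 103, and 30 × 103 = 3090. The formula is inferred: it gives 1770, not 1650, for the 4.0% versus 0.2% scenario, but nothing below depends on that.

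**2. AWP rate without rocuronium, odds-ratio route.** Let r be rocuronium use. Solve (1−r)p0 + r·p1 = 3.3%, with p1 = 6.05p0/(1 − p0 + 6.05p0).
- r = 60%: p0 = 0.85%, p1 = 4.9%
- r = 49%: p0 = 0.99%, p1 = 5.7%

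**3. Same rate from the counts.** 23 − 19 = 4 cases had no rocuronium, so p0 = (4/23) × 3.3%/(1−r) = 0.574%/(1−r).
- r = 49%: 0.574/0.51 = 1.13%
- r = 60%: 0.574/0.40 = 1.43%

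**4. How much hangs on r.** Use among the 620 patients (306 + 314) is not given, so 49–60% is an assumption. The direction is robust to it. The count route exceeds 0.6% once r is above 1 − 0.574/0.6 = 4%. On the odds-ratio route, p0 = 0.6% gives p1 = 3.52%, so r would have to reach (3.3 − 0.6)/(3.52 − 0.6) = 92% before p0 fell to 0.6%.

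**5. Power at 3090, control rate 3.3%.** If use falls by a fraction c, the intervention rate is (1−c) × 3.3% + c × p0. The simulation fits the planned logistic model (site and period fixed effects, 103 per cell, likelihood-ratio test, 2,000–3,000 runs, rejection under the null 5.2%).

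| Scenario | Intervention rate | Sizing formula | Simulated |
|---|---|---|---|
| Plan's input | 0.6% | 80% | about 91% |
| Full removal, odds ratio, r = 60% | 0.85% | 72% | 81–84% |
| Full removal, odds ratio, r = 49% | 0.99% | 67% | about 73% |
| Full removal, counts, r = 49% | 1.13% | 62% | about 65% |
| Full removal, counts, r = 60% | 1.43% | about 50% | about 49% |
| 80% fall, most favorable | 0.2 × 3.3 + 0.8 × 0.85 = 1.34% | 53% | about 55% |
| 80% fall, least favorable | 0.2 × 3.3 + 0.8 × 1.43 = 1.81% | 34% | about 32% |

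**6. Precision.** At the upper odds-ratio limit, 17.56, p0 is 0.3–0.4%; at the lower limit, 1.46, it is 2.6–2.7%. An odds ratio of about 9 (r = 60%) to 11 (r = 49%) would give 0.6%. For the crude count, 4 cases among 620 × 0.51 = 316 or 620 × 0.40 = 248 patients, the exact 95% intervals are 0.35–3.2% and 0.44–4.1%.

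**7. Higher control rate.** At 4.1%, full removal gives 1.07–1.24% by the odds ratio (power 81–77% by the sizing formula, 87–82% simulated) and 1.40–1.78% by the counts (72–59% by the sizing formula).

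**The case against.** Much of the opposing case stands.

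- A reader might infer that 3090 was miscalculated. It was not: step 1 reproduces it, and the planned model does somewhat better than 80% at the stated rates. The problem is an input.
- A reader might infer that the ED data rule out 0.6%. They do not: both intervals in step 6 include it.
- 3.3% is the lowest of the three ED rates in the Background (3.3%, 4.1%, 7.4%), which is a genuine cautious step. At 4.1% part of the shortfall goes.
- 0.6% is more cautious than 0.2%. If 0.2% were the full-adherence rate, 0.6% would correspond to (0.6 − 0.2)/(3.3 − 0.2) = 13% dilution. That is an allowance only relative to an operating-room figure; the ED estimates do not support 0.2% as the full-adherence rate.
- A reader might suspect that the misprinted 92.6% produced the 0.6%. Using it, 0.074 × 3.3%/(1−r) gives 0.48–0.61%, but the sample-size text cites operating-room data and never uses that percentage. The link is not shown.
- A reader might conclude that a non-significant result is likely. That depends on adherence, which the protocol does not forecast, and on the control rate.

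Fidelity monitoring may limit non-adherence, and the complier analysis addresses a different estimand. Neither restores intention-to-treat power lost to residual use.

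**Conclusion.** The concern holds as a fault in the justification, not in the arithmetic. On the protocol's ED point estimates, 0.6% is optimistic even with no rocuronium use and carries no allowance for non-adherence. At a 3.3% control rate, power with full removal is about 72% to 50% by the formula that reproduces 3090, or about 81–84% to 49% by simulated likelihood-ratio test. With an assumed 80% fall in use the simulated figure is about 55% to 32%.

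This rests on 49–60% baseline use, an adjusted odds ratio applied as if it were the population one, and a causal association. The last is itself uncertain, since one of the protocol's cohorts found none; without it the intervention would be expected to do less, not more.

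**What to change.** Keep N at 3090. In the Sample size justification:
- stop describing 0.6% as conservative and as accounting for non-adherence, and say that it is an operating-room figure;
- state that the 80% holds only if the intervention-phase rate is about 0.6% against 3.3%. Do not substitute another single threshold such as 0.85%: that reaches 80% under the simulated likelihood-ratio test but only 72% under the sizing formula;
- add a table of power over control rates of 3.3–4.1% and a range of achieved reductions in rocuronium use, naming the method and showing the uncertainty in the odds ratio;
- say that a non-significant result will be interpreted by its confidence interval.

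As a separate minor correction in the Background, change 92.6% to 82.6% (19/23 = 0.826).

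The cost is wording and one table, with a less favorable power statement and no extra patients. It should be done before results are known.

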**Fig. 1 Fig1:**
[figure not shown]
Important risk factors for awareness with paralysis include sedation under dosing, neuromuscular blocker use, and a lack of protocolled monitoring of sedation depth. Every major risk factor for awareness with paralysis commonly occurs in the emergency department

The data cited above provided our research group with the preliminary data to justify further study of AWP among mechanically ventilated ED patients. The ED-AWARENESS Study was a single-center, prospective cohort study which consecutively enrolled 383 mechanically ventilated ED patients over a 12-month period at a large academic medical center [19, 20]. Among survivors given NMB in the ED, the proportion of patients experiencing AWP was 3.3% (10/306; 95% CI, 1.6–5.9%) [19]. In an a priori secondary analysis of the multicenter ED-SED Pilot Trial, we demonstrated that 4.1% (13/314; 95% CI, 2.2–7.0%) of survivors that were given a NMB in the ED experienced AWP [21–23]. Finally, in a single-center prospective cohort conducted at Hennepin County Medical Center (an enrolling site for the current trial), the proportion of patients experiencing an AWP event was 7.4% (66/886; 95% CI, 5.8–9.4%) [24]. Taken as a whole, these data justify a clinical trial aimed at prevention of AWP among mechanically ventilated ED patients and strongly suggest the ED could be a high-yield arena in which to improve patient-centered clinical outcomes.

Psychological trauma and PTSD are a significant burden among the critically ill. PTSD is the development of significant distress or social impairment in someone directly or indirectly exposed to death, threated death, injury, or violence. Critical illness is psychologically traumatic, and 25–35% of survivors experience PTSD [25–27]. These survivors have worse quality of life, greater frequency of pain and substance abuse, increased healthcare cost, and threefold greater risk of death [28–33].

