However, similar to AWP, there is a significant knowledge gap with respect to critically ill, mechanically ventilated ED patients. Prior ED-based PTSD work has largely focused on traumatic injury or specifically excluded mechanically ventilated patients [34–37]. In a cohort study of 99 ED patients, our team demonstrated clinically significant PTSD symptoms in 31% of patients with acute respiratory failure, but only 9 patients (9.1%) were mechanically ventilated [38]. Therefore, the burden of PTSD in this cohort is unknown, and the ED could be an optimal target for improving mental health outcomes for several reasons. Critical illness-related mental health disorders are linked to exposures during care, and early frightful memories during illness are linked to higher PTSD prevalence [1, 26]. In addition, delays in care for PTSD are common and linked to refractory symptoms [6, 39–41]. This evidence suggests the early period of critical illness opens a window to reduce psychological morbidity in survivors. The ED-AWARNESS-2 Trial will inform creation of interventions to be used during (not after) an event to mitigate symptom development, and it will use the ED as a target in which to improve outcomes during the “golden hours” (Fig. 2) [34, 42].

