Instrumental variable (IV) methods will be used to account for non-adherence, as there could be differences between intervention effectiveness (i.e., effect among all patients to whom the intervention is targeted) and efficacy (i.e., effects among patients whose clinicians adhere to the intervention). We will use a non-parametric IV estimator adapted to stepped wedge designs, and IV regression methods to estimate complier average causal effect (CACE) of the intervention [79]. To avoid conflating the effect of time with the intervention effect, we will (1) obtain step-specific CACE estimates and (2) summarize step-specific estimates across all steps. We will also use two-stage residual inclusion to perform IV regression, using individual data from all six time points, adjusting for time and cluster effects [80–82]. Unlike per-protocol analyses, CACE analyses are not biased by selection effects and have been shown to be valid inferential approaches in stepped wedge trials [79].

We will determine proportion (with 95% CIs) of patients with clinically significant PTSD symptoms (PCL-5 score > 32) at 30 days and 180 days post-discharge [83, 84] and compare the control versus the intervention phase. To test the independent association of AWP (main exposure of interest) with 30-day PTSD symptom development, multivariable logistic regression will be used, with covariates selected for inclusion a priori [85]. The model will be adjusted for covariates previously associated with PTSD symptoms in critical illness survivors: (1) age; (2) sex; (3) prior psychological trauma (PC-PTSD-5 score)/mental health history; (4) illness severity; and (5) receipt and dose of benzodiazepines [10, 25, 26, 62, 86, 87]. We will adjust for race, given known racial disparities in PTSD symptoms [88–91]. To examine time trends in PTSD symptoms, and independent effects of AWP on time trends, mixed effect logistic regression will be used. Individual random intercept and random time slope will be specified and tested along with other potential risk factors. We will identify individual-level potential risk factors which could explain variation in individual time trend by testing interaction between random time slope and risk factor(s). In all of these models, cluster effect will be modeled as a fixed effect, using cluster indicator in the model. Similar analyses will be conducted for the other secondary outcomes.

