Relevant limitations exist. A fundamental challenge of pragmatic trials is designing a flexible yet effective intervention-adherence plan to enhance fidelity. To address this, we will employ a systematic and multifaceted intervention approach, similar to our prior pragmatic work that has been successful in ED-based studies. We will perform secondary efficacy (CACE) analyses among patients who would have received the intervention if assigned to it. The modest frequency of AWP may raise questions regarding the number of patients who may benefit. However, as AWP is so consequential to patients experiencing it, our results are expected to carry significant impact. Further, the entire cohort is at high risk to experience psychological morbidity. By rigorously assessing these outcomes in all patients, we will acquire new knowledge that could benefit all mechanically ventilated patients. The trial design includes follow-up beyond the index hospitalization, and incomplete follow-up is a potential problem. We acknowledge loss to follow-up rates ranging from 16 to 50% in prior critical illness-associated PTSD literature [62, 104]. With a response rate of approximately 40%, the sample size will still be large enough to achieve our aims. We will promote patient retention by making the patients aware of the follow-up calls at day 30, obtaining multiple contact numbers by which to reach them, and by messaging the patients to arrange the most appropriate day and time to call.

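### The AWP–PTSD analysis is sized on PTSD in 20% of patients without AWP, but the Background gives 25–35% from the same references; the stated 80% power depends on that unexplained choice

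*Protocol article*

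**What the plan says.** All places are in the protocol article.

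- **Sample size justification** sets the two rates: "if we estimate that PTSD occurs in 45% of those with AWP [5, 6, 9] and 20% of the rest of the cohort [25–27"]. It continues: "assuming *α* = 0.05 and power = 0.80, using two-sided *Z*-test with pooled variance, a sample size of 1192 patients will be required". The share of patients with AWP used in this calculation is not given. For the primary outcome the same section says "we will assume a prevalence of AWP of 3.3% in the control phase and 0.6% in the intervention phase".
- **Background** gives the PTSD rate in survivors of critical illness, with the same reference numbers: "Critical illness is psychologically traumatic, and 25–35% of survivors experience PTSD [25–27"].
- **Background** also reports the team's own ED cohort of 99 patients: "our team demonstrated clinically significant PTSD symptoms in 31% of patients with acute respiratory failure, but only 9 patients (9.1%) were mechanically ventilated". It concludes that the burden in ventilated ED patients is not known.
- **Proposed statistical methods** defines the endpoint: "We will determine proportion (with 95% CIs) of patients with clinically significant PTSD symptoms (PCL-5 score > 32) at 30 days" and at 180 days. The AWP association at 30 days is to be tested by multivariable logistic regression.
- **Discussion** addresses loss to follow-up, citing losses of 16–50% in earlier studies, and then says: "With a response rate of approximately 40%, the sample size will still be large enough to achieve our aims".

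**The concern.** One set of references supports two PTSD rates that do not overlap, and no reason is given for using the lower one. The patients without AWP are nearly the whole cohort, so their rate should be close to the survivor rate quoted in the Background. A lower comparator rate is not cautious here, because it enlarges the assumed difference from 45% and so reduces the required sample size.

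Two statements rest on it. One is the 80% power for the only PTSD comparison the protocol sizes. The other is the assurance about a 40% response, which works because 1,192/3,090 = 38.6%. If the comparator rate is really 25–35%, a null AWP–PTSD result could be reported as coming from an adequately powered analysis when it did not, and the tolerable loss to follow-up would be misjudged.

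**Working it through.** **Inputs.** From Sample size justification: p1 = 0.45 (with AWP), p2 = 0.20 (without), two-sided α = 0.05, power 0.80, Z-test with pooled variance, N = 1,192, total trial size 3,090. From Background: 25–35%, and 31% in the ED cohort. From Discussion: 40% response, so 0.40 × 3,090 = 1,236. The AWP share f is not stated and has to be inferred.

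**Step 1: reproduce 1,192.** With p̄ = f·p1 + (1−f)·p2,

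N = [1.96·√(p̄(1−p̄)(1/f + 1/(1−f))) + 0.8416·√(p1(1−p1)/f + p2(1−p2)/(1−f))]² / (p1−p2)²

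At f = 0.02, p̄ = 0.205. The two terms are 5.652 and 2.980, so N = 8.632²/0.25² = 1,192. Solving for f gives 2.00%. The midpoint of the plan's 3.3% and 0.6% is 1.95%, which gives 1,222. A share of 3.3% gives 737. The plan's figure therefore corresponds to about 2% AWP, or 0.02 × 1,192 ≈ 24 AWP patients.

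**Step 2: can excluding AWP patients explain 20%?** If 25% of all survivors have PTSD, the rest have (0.25 − 0.02 × 0.45)/0.98 = 24.6%. If 35%, the rest have 34.8%. Conversely, 20% in the rest implies 20.5% overall. The exclusion moves the rate by less than half a point.

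**Step 3: vary the comparator, holding 45% and f = 2%.**

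Power = Φ[(|p1−p2| − 1.96·SE0)/SE1], where SE0 = √(p̄(1−p̄)(1/f + 1/(1−f))/N) and SE1 = √((p1(1−p1)/f + p2(1−p2)/(1−f))/N).

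- At 25%: (0.20 − 1.96 × 0.0901)/0.1027 = 0.23, so power is 59%.
- At 35%: (0.10 − 1.96 × 0.0988)/0.1028 = −0.91, so power is 18%.

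| PTSD without AWP | Power, N = 1,192 | Power, N = 1,236 | Power, N = 3,090 | N for 80% |
|---|---|---|---|---|
| 20% | 80% | 81% | 99% | 1,192 |
| 25% | 59% | 60% | 92% | 2,060 |
| 30% | 36% | 37% | 70% | 3,944 |
| 31% | 32% | 33% | 64% | 4,583 |
| 35% | 18% | 19% | 37.5% | 9,360 |

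At 25%, the 2,060 needed is 67% of 3,090. At 30% and above, complete follow-up would not reach 80%.

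**Step 4: let the AWP-group rate move instead (N = 1,192, f = 2%).** 45% against 20% is an odds ratio of (0.45/0.55)/(0.20/0.80) = 3.27.

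| Without AWP | AWP rate at OR 3.27 | Power | AWP rate at +25 points | Power |
|---|---|---|---|---|
| 25% | 52% | 82% | 50% | 76% |
| 30% | 58% | 83% | 55% | 73% |
| 31% | 60% | 83% | 56% | 73% |
| 35% | 64% | 83% | 60% | 71% |

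**Step 5: detectable AWP-group rate.** With 1,236 responders and a 1.95% AWP share (about 24 AWP patients), 80% power requires an AWP-group rate of about 51%, 57%, 58% and 63% for comparators of 25%, 30%, 31% and 35%.

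**The case against.** The strongest reply is that the fall in power comes from changing one rate and freezing the other. The planned model is a logistic regression, whose parameter is an odds ratio. At an odds ratio of 3.27 power stays at 82–83% across the whole 25–35% range (Step 4), and at a constant 25-point difference it is 71–76%. This stands. A reader might infer that the analysis has 18–59% power and not 80%, as a plain fact. The documents do not support that, because the result depends on holding 45% fixed. But 45% is the only AWP-group rate the plan gives, and it states neither a constant odds ratio nor an AWP-group rate of 52–64%.

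Other points that stand in part:

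- The arithmetic is right: 1,192 reproduces. The problem is an unexplained input.
- The 2% AWP share is inferred. At 3.3%, power at 1,192 with 45% fixed would be 78% (25%) down to 26% (35%), but the plan's N would then have been 737.
- A reader might infer that 31% is the correct comparator. It is supporting evidence only, since 9 of those 99 patients were ventilated. The cited references cannot be consulted here, so a cohort-specific reason for 20% cannot be ruled out. None is given.
- A 40% response is the plan's low case. Losses of 16–50% would leave 1,545 to 2,596 responders, with power of 69–88% at a 25% comparator and 22–33% at 35%, again with 45% fixed.
- The analysis is secondary and concerns a non-randomised exposure, and no trial decision depends on it.

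**Conclusion.** The point holds as an unreconciled planning assumption. The protocol uses 20% where its own Background gives 25–35% from the same references. Removing AWP patients cannot account for the difference, and the choice favours the stated sample size. With the plan's 45% held fixed and the inferred 2% AWP share, power at 1,192 is about 59% at a 25% comparator and 18% at 35%, and 60% and 19% at a 40% response. At that share, the stated 80% survives across the range only if the AWP-group rate also rises to about 52–64%, which the plan does not state. These figures apply to the plan's own unadjusted Z-test, not to the covariate-adjusted model. The claim that a 40% response is enough is therefore not secured for this analysis. The primary comparison and its 3,090 patients are untouched.

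**What to change.** Reconcile Background and Sample size justification in one of two ways.

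1. Keep 20%, and state why it applies to a PCL-5 score above 32 in this cohort when the Background gives 25–35%.
2. Restate power over 25–35%, giving the AWP share used, the assumption held fixed (the 45% rate or the odds ratio), and the detectable rate. For example: with about 1,236 responders, about 24 of them with AWP, power for 45% against 25–35% is about 60% down to 19%, and the AWP-group rate detectable with 80% power is about 51–63%.

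In Discussion, qualify the statement on a 40% response so that it does not cover this analysis unconditionally. Report the AWP–PTSD odds ratio with its confidence interval, and do not describe a null result as adequately powered.

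The cost is a few sentences and, under the second option, a less favourable power statement for a secondary analysis. No patients, visits or data are added.
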